### Study Population and Recruitment

This study will specifically target lower active employees (<10,000 steps per day). Hospital employees (including health care professionals and administrative and business support personnel) enrolled in the Change4Life program will be invited to participate via website notifications and hospital newsletters. Only data from participants who accumulate less than 10,000 steps per day during the “2-Week Run-In” period will be included in the analysis. Further eligibility criteria will include: 18 years of age or older, English speaking, ready Internet access, and without medical conditions exacerbated by physical activity as assessed by the Physical Activity Readiness Questionnaire Plus. Eligible participants will be asked to provide their expressed consent using the online consent form.

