### Outcome Measures

The primary study outcome will be the mean proportion of participant-days that step goals are achieved during week 24 (the postintervention follow-up assessment period, T3). Mean proportion of participant-days that step goals are achieved during week 12 (intervention end point, T2) and volume of steps and 10-minute bouts of MVPA per week at T2 and T3 will be secondary outcomes. Physical activity will be objectively assessed using the StepsCount Piezo Rx accelerometer (StepsCount Inc, Deep River, ON, Canada). The Piezo Rx is a medical-grade device with a single axis piezoelectric sensor. This device has been found to be valid in calculating step counts and MVPA among adult participants [35,36]. Standard care and intervention participants will be encouraged to wear their accelerometer and synchronize it to the Change4Life program during the baseline 2-Week Run-In period (T1), as well as at the intervention end point (T2), and follow-up assessment (T3) with Can $10 (US $7.40) study retention vouchers; these vouchers for assessment completion will help minimize dropout and will not be contingent on step goal achievement.

The adherence outcome variables will be mean number of missing step count entries per week as well as mean number of Change4Life website log-ins in general. Participants’ self-determined motivation to exercise will be examined using the Behavioral Regulation to Exercise Questionnaire-3 (BREQ-3) [37,38]. Participants’ walking self-efficacy will be assessed using a modified version of the Self-Efficacy for Exercise Scale (SEE Scale) [39]. The BREQ-3 and the SEE Scale will be administered online at baseline (T1), intervention end point (T2), and during the follow-up assessment period (T3). The differential impact of the Can $1 (US $0.74) per day incentive on the various physical activity outcomes will be explored. For instance, we may find that while the guaranteed incentives stimulate step goal achievement at T2, they also undermine self-determined motivation and thus the prospect that people will continue to exercise after the incentive is removed.

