### Randomization and Blinding

Employees accumulating fewer than 10,000 steps per day during the baseline period (study weeks 1 and 2) will be randomized using a single, constant allocation ratio (1:1) to standard care or intervention groups. Randomization will occur using an online random number generator [40]. Participants will not be blinded to study group allocation. The research analysts will be blinded to group allocation until after the study is completed.

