### Statistical Analyses

For each participant on each day of the study (participant-day level) continuous step count data will be obtained and screened for outliers (less than 100 steps per day, more than 50,000 steps per day) [31]. If participants did not synchronize their accelerometer for at least 3 separate workdays at T2 and T3, the last observation will be carried forward using T1 or T2 means [33]. This procedure conservatively assumes no change in variables and allows analysis by intention-to-treat. The step count data will then be dichotomized at the participant-day level to create a binary variable where participants achieved (value = 1) or did not achieve (value = 0) their step goal. Using this binary variable, the mean proportion of participant-days where step goals were achieved at week 24 will be compared.

SPSS version 21.0 (IBM Corp) will be used to fit a generalized linear model with participant random effects, a random intercept, time-fixed effects (T1-T3), and treatment-fixed effects (by study group). A binomial distribution with logit link for models using the binary outcome will be used to estimate the adjusted difference in the proportion of participant-days step goal achieved, and the bootstrap procedure and resampling of participants will be used to obtain 95% confidence intervals and *P* values. Comparisons across study groups will be adjusted for mean steps per day (baseline), age, gender, and income since these have moderated incentive-effects in the past [41]. The same procedures will be used to analyze T2 (ie, intervention end) binary data.

For continuous step count (ie, mean steps per day) and bout minutes (ie, total minutes of MVPA in 10-minute bouts per week) data at T2 and T3, a generalized linear model will be used, as above, except the difference in steps per day and MVPA bout minutes between groups will be obtained using least-squares means. Also, a repeated measures analysis of variance using linear mixed models with first order autoregressive covariance structures will be used to compare changes in self-determined motivation and self-efficacy between groups. Adherence will be analyzed using *t* tests comparing the mean number of missing step count entries per week and mean number of website log-ins per month between groups. This protocol is registered with ClinicalTrials.gov [NCT02638675].

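### The t test for missing step entries leaves each participant's run-in value of the same measure unused; it is a valid test that gives up some precision

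*Protocol article*

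**What the plan says.** The article's Outcome Measures section defines adherence by two measures: "The adherence outcome variables will be mean number of missing step count entries per week as well as mean number of Change4Life website log-ins". Statistical Analyses then fixes the method, t tests "comparing the mean number of missing step count entries per week and mean number of website log-ins per month between groups", and names no covariate for them.

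The same section treats the other outcome families differently. The model for step-goal achievement is "adjusted for mean steps per day (baseline), age, gender, and income". Steps and MVPA bout minutes follow the same modelling approach. Motivation and self-efficacy, measured at T1, T2 and T3, get a repeated-measures mixed model.

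On timing, Outcome Measures has both arms wearing and synchronizing the accelerometer in the two-week run-in (T1), with a retention voucher. Randomization and Blinding places allocation after that period: "Employees accumulating fewer than 10,000 steps per day during the baseline period (study weeks 1 and 2) will be randomized". Under Standard Care Group, the platform calculates the baseline step average at the start of week 3 from the uploads of the previous two weeks. On log-ins, Study Population and Recruitment says only that employees "enrolled in the Change4Life program will be invited to participate via website notifications and hospital newsletters".

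**The concern.** A participant's synchronization record in weeks 1 to 2 is a baseline measurement of the missing-entries outcome. It is taken before allocation and is held by the platform that will supply the outcome. People who skip uploads in the run-in may well skip them later. To the extent that they do, a plain t test leaves predictable between-person variation in the error term, which widens the interval for the group difference and lowers power.

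The stake is modest but real. The Limitations section expects that participants, especially in standard care, may stop synchronizing. Missing uploads at T2 and T3 also trigger the carry-forward rule under Statistical Analyses. A more precise estimate of the difference in missing entries would therefore help in reading the trial, although it would not alter the primary analysis.

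**Working it through.** **Inputs from the protocol article.** 79 per group analysed, 80% power, two-sided 0.05, and 0.40 versus 0.20 for the primary outcome (Sample Size); 1:1 allocation (Randomization and Blinding).

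**Input not in the article.** rho, the correlation between a participant's run-in missing-entry rate and the later rate. It is an assumption and is shown as a range.

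**Step 1: reproduce the plan's own figure.** With the unpooled normal approximation for two proportions, n per group = (1.960 + 0.842)² × (0.40 × 0.60 + 0.20 × 0.80) / 0.20² = 78.5, which rounds up to 79. This matches. The figure belongs to the primary outcome; none is given for adherence.

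**Step 2: set an illustrative base.** With 79 per group, the standardized difference that a t test detects with 80% power is 2.802 × √(2/79) = 0.446 SD. This is a yardstick only, because the plan states no target difference for adherence.

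**Step 3: adjust for the run-in value.** Linear adjustment multiplies the residual variance by 1 − rho², so

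power = Φ(2.802 / √(1 − rho²) − 1.960).

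| rho | 1 − rho² | power |
|---|---|---|
| 0 (t test) | 1.00 | 80.0% |
| 0.1 | 0.99 | 80.4% |
| 0.2 | 0.96 | 81.6% |
| 0.3 | 0.91 | 83.6% |
| 0.5 | 0.75 | 89.9% |
| 0.7 | 0.51 | 97.5% |

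**Step 4: find where the gain reaches 5 points.** Power of 85% needs 2.802 / √(1 − rho²) = 1.960 + 1.036 = 2.996. Then 1 − rho² = (2.802/2.996)² = 0.875, and rho is about 0.35.

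**Step 5: the same result on other scales, at rho 0.5.** The t test would need 79 / 0.75 = 105 per group to match the adjusted analysis. The detectable difference falls from 0.446 to 0.446 × √0.75 = 0.386 SD.

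**Step 6: check with a bounded count outcome.** A simulation was run with assumed inputs: 79 per group, 14 run-in days, 70 follow-up days, and 2,000 runs per setting. Power for the t test versus the adjusted linear model was 38% versus 44% at rho of about 0.43, 54% versus 72% at about 0.56, and 73% versus 95% at about 0.71. With no group effect, rejection rates were 5.3% and 5.1%. The direction agrees with the formula, and both analyses hold their level.

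The formula credits only the run-in value, assumes a linear relation, and ignores the few degrees of freedom spent on covariates. At rho of 0.1 the result is best read as no change.

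**The case against.** The strongest reply is that nothing is wrong with the planned test. Under 1:1 randomization a t test is unbiased with correct type I error. A reader might infer that chance imbalance in earlier engagement contaminates the estimate. It does not do so in any sense that the standard error fails to cover. This stands: the issue is precision only.

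Second, adherence is neither the primary outcome nor among the named secondary outcomes, and it has no power target. The 80% base is therefore hypothetical, and nothing shows that the comparison is underpowered. This stands too. A reader might also infer that the adherence tests are the trial's safeguard against differential engagement distorting the step results. The protocol gives them no such role. Limitations answers possible dropout with retention vouchers, and a sharper test of missingness would leave the carry-forward rule as it is.

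Third, rho may be low. The run-in is two weeks long and voucher-supported, and participants must supply run-in step data to be confirmed as lower active and to receive a goal. All of this narrows the spread of run-in missingness. This stands as a limit on the size of the gain.

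Fourth, one might say that both adherence measures have a baseline ready for use. The documents do not support that for log-ins. Prior enrolment implies a log-in history, but no section says that counts from before randomization are recorded or extracted.

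What survives is narrow. For missing entries the baseline exists before allocation, the planned method cannot use it, and using it does no material harm even when it predicts little.

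**Conclusion.** The point holds as a minor efficiency remark, firm for missing step entries only. The planned t test is valid; adjusting for the run-in rate would estimate the same kind of group difference more precisely. The benefit runs from practically nothing at rho of 0.2 or less, through 5 points of power at about 0.35, to roughly 10 points at 0.5. All of these figures are measured from an assumed 80% base with 79 per group. The documents do not fix rho, and the design of the run-in gives reasons to expect the lower part of that range for this outcome. For log-ins the point is conditional on data that the protocol does not say it has. Nothing here affects the primary comparison.

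**What to change.** Under Statistical Analyses, replace the t test for missing entries with a regression of mean missing entries per week, counted after randomization, on group, the participant's run-in missing entries per week, and the covariates already named (baseline steps, age, gender, income). Report the adjusted group difference with a 95% CI. Missing entries per week is a bounded count (0 to 7), so use robust or bootstrap standard errors with the linear model, or a count model.

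Apply the same approach to log-ins per month only if log-in counts from before randomization can be extracted from the platform. Otherwise leave that comparison as it is.

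The cost is a sentence of analysis wording, derivation of the run-in rate from uploads already held, and slightly more analysis work. There is no new data collection for missing entries. The downside is that the return will be small if rho turns out to be low.

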## Results

Enrollment for the study will be completed in February 2017. Data analysis will commence in September 2017. Study results are to be published in the winter of 2018.

## Discussion

### Overview

Physical activity maintenance is critical for controlling the human and economic burden of chronic disease [1,2]. While incentives have stimulated physical activity behaviors in the past [20-26], only 1 RCT to our knowledge has produced longer term, postintervention improvements [25]. The primary aim of this protocol is to outline the design of an RCT to test whether adding theoretically informed guaranteed incentives to an existing physical activity promotion program can drive physical activity for 12 weeks after guaranteed incentives are removed in a workplace context. Since one of the risks with incentives is that they damage self-determined motivation and thus people’s potential for sustained change [42], the theoretical considerations in this study extend beyond behavioral economics (which merely describes how incentives may be used as a catalyst for change) [19] to include insights from self-determination theory (which describes the conditions under which incentives may produce sustained change) [29]. The literature examining the undermining effect of incentives has mostly considered simple tasks for which initial intrinsic motivation is high, although these findings should not be generalized to lifestyle health behaviors like physical activity where initial intrinsic motivation can be low [43]. In addition, incentive schemes vary greatly in their design and can differentially moderate the undermining effect [43]. While more research is needed, schemes that target less active adults for realistic behavioral outcomes are theorized to support the internalization process and promote quality behavior change [29,30].

According to self-determination theory, incentives may help to build self-determined motivation primarily through their action on self-efficacy, especially for lower active people who exhibit fewer intrinsic motives to begin with (less motivation to crowd out) [44,45]. Regarding physical activity, one hypothesis is that incentives may increase a person’s self-efficacy to become more active by exposing them to a form of physical activity for the first time [29,30,44,45]. Especially if the activity is an achievable one (eg, walk 1000 more steps per day vs walk 10,000 steps per day), individuals may find their confidence to be more active increases after just a few weeks [29,30,44,45]. To align with self-determination theory, then, we decided to (1) target lower active employees only (because they have less/little self-determined motivation to crowd out) [23,24,29] and (2) offer incentives contingent on tailored/realistic step goal achievements (to maximize mastery experiences and increase self-efficacy) [45]. The main theoretical contribution of this protocol therefore is in its application of self-determination theory to the design of the incentive intervention (ie, realistic behavioral targets) and program evaluation (ie, tracking motivation throughout).

The practical implications of this research are also important given the growing popularity of incentive-based wellness programs [42]. First of all, we hope the results of this RCT encourage others to incorporate a simple but important incentive program design nuance by offering rewards contingent on tailored, rather than generic, physical activity goals. The pervasiveness of wearable physical activity monitors in general (eg, smartphones with built-in accelerometers) may make it easier for interventionists or employers to individualize physical activity goals in the context of a health rewards system (by setting goals based on an individual’s own physical activity pattern). Another practical implication of this study may be in encouraging employers to consider guaranteed rewards systems for higher-risk, higher-cost employees only versus the traditional (and largely ineffective) approach of offering low-frequency, low-magnitude chance-based rewards to everyone. To manage budgets, employers often opt for the seemingly more affordable chance-based reward scheme even though there is limited evidence of its effectiveness [20]. Finally, if incentives are not amenable to employees, the intervention will almost certainly fail [46]. Employers deploying incentives should therefore consider any unintended consequences of this novel approach, including (1) perceived unfairness (eg, Why should only lower active employees be rewarded to exercise?), (2) opportunity cost concerns (eg, Should we really be spending money on this?), (3) gaming/cheating (eg, I will cheat by getting my friend to track my activity for me), and (4) low overall acceptability (eg, I don’t want my employer telling me what to do) [47-49]. One way of circumventing the perceived unfairness issue may be in offering minimal chance-based rewards to all employees regardless of physical activity level as well as an enhanced incentive program to employees qualifying as lower active or higher-risk. Supporting such an approach with empirical data may alleviate concerns around unfairness, opportunity cost, and acceptability as well [47-49].

### Limitations

This study protocol is not without limitations. First, given that only employees already enrolled in Change4Life (less than 10% of the eligible employee population) will be assessed for eligibility and invited to participate in the study, the results may not be generalizable. By recruiting only lower active Change4Life enrollees, we will learn more about how a higher risk employee population responds to incentives. Since the hallmark of Web-based health interventions is low engagement [49], there is potential for significant study dropout as well (ceasing daily device synchronization and not participating in assessments), especially among standard care participants. Both intervention and standard care participants will be encouraged to participate in all scheduled assessments (baseline, intervention end point, follow-up) with Can $10 (US $7.40) vouchers. Given the low participant burden and potential for lower active individuals to experience improved health, however, this voluntary incentive-based wellness program may be met with relatively high levels of engagement. Finally, participants will not be blinded to study group allocation, which could contaminate the results. Knowledge of group allocation will be assessed using a study exit survey to monitor this potential confounder.

### Conclusion

The objective of this study is to improve the longer term maintenance of physical activity through a better understanding of how to structure and evaluate incentive programs. Incentives are not a panacea, of course, and may not work for all people, but as part of broader package of interventions and under certain conditions incentives may have a role to play in driving sustained health behavior change.

## Abbreviations

BREQ-3: Behavioral Regulation to Exercize Questionnaire
MVPA: moderate-vigorous physical activity
SEE: Self-Efficacy for Exercise
